### Blinding

The medical and psychological assessments are blinded as these precede randomization. After assignment to interventions, the outcome assessors (study nurse and site investigators) and principle investigator will be blinded. While patients and parents will be blinded, blinding of trainers in the treatment is not possible. However, trainers are not involved in the assessment process.

Group allocation will be coded by different letters; only the trainers and the administrator of randomization results will be informed about the corresponding intervention.

The primary outcome will be reported by the children themselves, who are not aware of their respective treatment allocation. Assessment of data is blinded on all points of measurement. Follow-up data will be assessed by telephone interviews (blinded interviewer) with the younger children and questionnaires for older children and the parents. Information material and questionnaires in the follow-up phase will be sent out directly to the participating families. Data collection and data analysis are independent. Data entry is operated by computer scanning and is therefore blinded.

Early unblinding is not intended. Regular unblinding occurs after complete data collection, that is, after the last data of T4 is collected and entered into data set. Process data of the intervention-specific pain diaries will be added to the data set after all other data are entered and therefore constitutes the first step of unblinding.

### Stopping rules

For the individual patient, it is stated that children can discontinue treatment in case of observed unusual, continued and increased, severe bodily complaints or in case of red flags. Then, the study physician will be consulted, and diagnostics and treatment are advised. The whole intervention will be stopped in case of occurrence of severe adverse effects in association with the intervention in more than 5% of the children. A study center will be closed when it fails to meet or adhere to the study protocol in more than three cases in a row, or if for two consecutive time spans, fewer than three children could be included in the study over the course of 3 months.

### Ethical approval

This trial was approved by the Ethics Committee of the University of Potsdam and the responsible ethics committees/state chambers of physicians of the five study centers. A list of ethical bodies can be found in Additional file 1.

All study staff commit themselves to the Declaration of Helsinki (Version 2013), as well as to all pertinent national laws and the ICH guidelines for GCP issued in June 1996 and CPMP/ICH/ 135/95 from July, 2002. Important protocol modifications will be reported to all relevant parties.

### Data safety

Staff working in this trial will be bound by the duty of confidentiality. The respondents’ privacy and anonymity is safe-guarded as personal patient data will be stored in a restricted room separately from the questionnaires. The latter are coded in an anonymous way before their transfer to the central study office where data entry and analysis will take place. All personalized data (addresses) are destroyed after the termination of follow-up. The participating treatment facilities will only receive aggregated statistical data as feedback. All potential study participants receive adequate written information about the aims and implications of the study before consent is given. Informed consent will be obtained from children and their parents by the site investigators.

### Data analytic plan

Missing values will be replaced by unbiased substitution (EM-algorithm). Data will be analyzed by intention to treat (ITT) supplemented by a per protocol analysis (PPA) to test for effects of treatment adherence.

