### Sample size - power analysis

The calculations rely on the high effect size of our primary outcome (d = 1.09 for the composite pain score; see [21, 22]) and correlation among repeated measures 0.8 (see [20–22]). Since our recent single-site study included a 3-month follow-up and a waiting list control group (instead of an active control group [21, 22]), power analysis for the primary outcome is based conservatively on a medium effect size (f = 0.25; d = 0.6). Independent variables are intervention (2), gender (2), age (2) and site of intervention (5), forming a total of 2^3^*5 = 40 groups.

In the study centers, n = 450 children will be assessed for eligibility and a total number of n = 112 children will be allocated to the trial (n = 56 in IG, n = 56 in CG). We assume a drop-out rate of 20% [cf. 18], resulting n = 112 children to be analyzed in the intention-to-treat analysis (ITT) and n = 90 children for the per protocol analysis (PPA).

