#### Drop-out rate

In our pilot study we did not observe drop-out of patients. In 9 out of 10 intervention studies, drop-out rates are below 25% [18]. We assume a loss of 20% due to drop-outs during the follow-up time span (cf. [40]). To prevent selective drop-out and incomplete outcome data, all participants will be reimbursed for completely filling in the questionnaires and the pain diary in the follow-up period.

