### Randomization

Allocation sequences are generated centrally at the Institute of Epidemiology at University Clinic of Hamburg-Eppendorf (KW). It will be mutually randomized in IG and CG with a 1:1 ratio. Each patient’s position on allocation sequence is defined by computer-generated random-numbers and the date of informed consent (chronologically sorted).

As groups are assigned parallel and the interventions are to be carried out mutually, blocking is dependent on the group sizes. Block sizes range between 6 and 16 patients. The total number of each block is dependent on the total number of groups to be trained. As in this trial, a maximum of 25 groups are to be trained; the number of blocks of 6 and 8 patients is restricted to five each.

The randomization procedure, in order to prevent selection bias, occurs centrally at the University of Potsdam by a person not involved in the intervention process and data analysis. We realize a stratified (according to center) block randomization. Randomization and allocation to interventions occur after assessment of pre-data and before the interventions start. Results of randomization will be provided directly only to the trainers via email (allocation concealment). Each center has to realize four different groups; at the first block of interventions, the trainer may choose the trial arm (IG versus CG); in the second block, the trainers have to change the trial arm.

The effectiveness of the randomization is evaluated post-hoc by descriptive statistical comparisons between IG and CG in known and presumed baseline predictors of treatment success (for example, pain history of the parents and socio-economic status) and relevant sociodemographic data (age and sex).

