### Exploratory analyses

We will also explore subscales of the outcome measures to see if there are indicators of treatment effects within these subscales.

In further exploratory analyses, we will include other baseline predictors in the model and explore their potential effect modification; moreover the effect of time-varying predictors will also be investigated. In a sensitivity analysis, we will explore the effect of missing values using various imputing methods (best and worst observation carried forward, last observation carried forward, full-information maximum likelihood and multiple imputation).

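### The stated EM substitution, read as a single fill, ignores imputation uncertainty in the confirmatory ANCOVA: depending on whether arm is in the EM model, the test is too liberal or the effect is diluted

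*Protocol article*

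**What the plan says.** All places are in the protocol article.

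- **Data analytic plan.** The rule for missing data is "Missing values will be replaced by unbiased substitution (EM-algorithm". The next sentence reads "Data will be analyzed by intention to treat (ITT) supplemented by a per protocol analysis (PPA".
- **Sample size - power analysis.** After 20% drop-out the text still has "resulting n = 112 children to be analyzed in the intention-to-treat analysis (ITT", next to "n = 90 children for the per protocol analysis (PPA".
- **Drop-out rate.** "We assume a loss of 20% due to drop-outs during the follow-up time span". The section adds that the pilot saw no drop-out and that families are reimbursed for complete follow-up data.
- **Primary analysis of the primary endpoints.** The primary test is an ANCOVA in the ITT population on the log area under the pain-intensity curve up to 12 months, adjusted for baseline.
- **Confirmatory analysis.** This test is the gate for the number and length of pain episodes. An alpha of 2.5% is given, and the overall level is said not to exceed 5%.
- **Analysis of secondary outcomes.** A mixed model is also planned for the primary and secondary outcomes.
- **Exploratory analyses.** Several other ways of handling missing values are listed as sensitivity analyses, among them "full-information maximum likelihood and multiple imputation".

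**The concern.** The EM algorithm estimates means and covariances. Substituting from it, without further steps, puts each missing value at its conditional mean. Such values have no residual scatter, and the ANCOVA then counts them as full observations. No section states a correction to the standard error, and none says whether treatment arm belongs to the EM model. That choice decides which of two problems arises:

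- **Arm in the model.** The estimate is unbiased, but the standard error is too small and the test rejects too often.
- **Arm not in the model.** Imputed values are pulled towards the pooled mean. Test size stays about right, but the treatment difference shrinks.

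At stake is the one test that opens the confirmatory hierarchy, and with it the claim that the overall alpha stays within 5%. This is not detail left to an analysis plan: the article names the method and describes it as unbiased.

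**Working it through.** **The plan's own figures.** 112 × 0.8 = 89.6, rounded to 90, which matches the per-protocol number. Then 112 − 90 = 22 children with some outcomes missing. Allocation is 1:1 ("It will be mutually randomized in IG and CG with a 1:1 ratio"), so 56 per arm.

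**AUC weights.** With T2, T3 and T4 at 0, 3 and 12 months, the trapezoid rule gives 1.5, 6 and 4.5 out of 12, that is 0.125, 0.5 and 0.375. T3 and T4 together carry 0.875.

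**Analytic check, all follow-up lost, arm in the model.** Let σ² be the ANCOVA residual variance.

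- Filled children add almost nothing to the residual sum of squares, so the residual variance is estimated at about 0.8σ².
- Reported SE² ≈ 4 × 0.8σ²/112. True SE² ≈ 4σ²/89.6.
- The ratio is 0.8 × 89.6/112 = 0.64, so reported SE / true SE = 0.8.
- Actual size at nominal 5%: 2 × [1 − Φ(0.8 × 1.96)] = 2 × [1 − Φ(1.568)] = 0.117.
- With arm left out, the filled children carry no treatment contrast, so a true 0.60 SD is estimated at 0.8 × 0.60 = 0.48.

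**Simulation.** 56 per arm, compound-symmetric normal data, 22 of 112 children lost completely at random with monotone drop-out, the AUC weights above, ANCOVA on baseline, EM conditional-mean fill, two-sided tests. Each setting had 3,000 null and 1,000 alternative data sets. The T3-and-T4 row comes from a separate run of similar design with 1,500 null and 500 alternative data sets and a true effect of 0.50 SD. The correlation of 0.8 is the plan's; 0.5 is added as a range.

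| Lost | Size at nominal 5%, arm in EM, r = 0.8 | Same, r = 0.5 | Mean estimate, arm not in EM, r = 0.8 |
|---|---|---|---|
| T4 only | 5.6% | 6.4% | 0.59 of 0.60 |
| T3 and T4 | 7.3% | 9.5% | 0.45 of 0.50 |
| Mixed times | 8.2% | 8.5% | 0.54 of 0.60 |
| T2 to T4 | 11.6% | 11.3% | 0.48 of 0.60 |

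For 3,000 runs the Monte Carlo SE at 5% is √(0.05 × 0.95/3000) = 0.4 points, so 5.6% is 1.5 SEs from nominal.

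- **Nominal 2.5%, arm in the model, r = 0.8:** 3.3% (T4 only), 4.8% (mixed), 7.2% (T2 to T4). Across the settings checked the ranges are 3.3-3.6%, 4.7-5.2% (mixed, or T3 and T4) and 7.1-7.5%.
- **Arm not in the model:** size at nominal 5% was 4.3-5.4%.
- **Standard errors, arm in the model, r = 0.8 (T4 only, mixed, T2 to T4):** reported 0.092, 0.087, 0.083; true sampling SD 0.093, 0.098, 0.104. The ratios are 0.99, 0.89 and 0.80.
- **Single fill with a random residual added:** 6.4%, 7.6% and 12.4% at nominal 5%, so restoring scatter alone does not cure it.
- **Multiple imputation** (20 imputations, arm in the model, Rubin's rules, r = 0.8, 700 runs, Monte Carlo SE about 0.8 points): 6.0%, 4.0% and 6.3% at nominal 5%; mean SEs 0.094, 0.099 and 0.103, in line with the true values.

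**The case against.** **That the fill is made once is an inference.** This is true. But the verb is *replaced*, and multiple imputation and full-information maximum likelihood are listed separately as sensitivity analyses, so the primary method is most naturally a single fill.

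**A reader might infer that the p-value and interval are wrong on any reading, or that both harms occur together.** The document does not support that. The harms are alternatives: with arm in the model the estimate is unbiased, and without it the p-value is roughly valid.

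**A reader might take 12% as the expected error rate.** That figure needs all 22 children to miss every post-baseline diary. The Drop-out rate section places the loss in the follow-up period, T2 is collected at the centres, and the pilot had no drop-out. If only T4 is lost and r = 0.8, the inflation is within Monte Carlo error. Loss of the mailed T3 and T4 diaries is the more realistic middle case.

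**At 2.5% the trial's 5% ceiling may still hold.** If that level governs the log-AUC test, which the wording leaves unclear, T4-only loss stays below 5%, and mixed or T3-and-T4 loss lies at about 5%. The test still does not have the size it claims.

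**The mixed model and the sensitivity analyses are already planned.** They soften the problem. The article does not say whether the mixed model runs on EM-filled data, and neither replaces the confirmatory test.

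**Counting 112 in the ITT analysis is ordinary practice.** Agreed; that number is not a fault. The fault is treating filled values as observed.

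**Conclusion.** The point holds in conditional form. As stated, the primary handling of missing data does not carry imputation uncertainty into the confirmatory ANCOVA, and *unbiased* is not a safe description of it. With arm in the EM model, size at nominal 5% is about 5.6-6.4% (T4 lost), 7-9.5% (T3 and T4 lost, or mixed) and 11-12% (all follow-up lost, the extreme). Without arm, the effect is understated by about 2%, 10% and 20% in the same order, with size near nominal.

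The figures rest on data missing completely at random, normality, compound symmetry with r = 0.5-0.8, AUC on the linear rather than the log scale, two-sided tests and the assumed drop-out times. None of these except r = 0.8 and the 20% loss comes from the document.

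A reader might also infer that the fill will produce negative or fractional counts for the Poisson model, or non-positive AUCs before the log. That could happen if the EM model is normal on the raw scale. The article does not state the scale and this was not simulated, so it remains a possibility, not a demonstrated error.

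**What to change.** In the Data analytic plan section:

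1. Make multiple imputation the primary handling for the log-AUC ANCOVA, with arm, baseline and all visits in the imputation model and Rubin's rules for pooling. An equivalent likelihood-based analysis of the observed data would also serve.
2. Move the single EM fill to the sensitivity analyses and delete *unbiased*.
3. State the scale on which diary values and counts are imputed.

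The log-AUC ANCOVA and the Poisson model need not be replaced to cure this defect.

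The cost is a change of wording: the article already names both methods, and it can be made before the planned unblinding after T4. Confidence intervals become wider. From the standard errors above, 0.094/0.092, 0.099/0.087 and 0.103/0.083 give about 2%, 14% and 24% for T4-only, mixed and complete loss. That is the width the observed data support.

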### Primary analysis of the primary endpoints

An analysis of covariance will be performed in the ITT population, comparing the log area under the pain intensity curve from intervention to 12-month follow-up between the two random groups adjusted for the baseline measurements. Length of pain episodes will be analyzed analogously. Frequencies will be analyzed using a Poisson regression model.

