#### Medical screening

Inclusion criteria include the following:age 7 to 12 years,Rome III criteria for FAP (that is, abdominal pain at least once per week for at least two months), andunexplained cause for abdominal pain.

Exclusion criteria include the following:insufficient German language skills,mental retardation,physician-ordered medication or therapy (psychological, pharmacological) of gastrointestinal complaints at the screening visit,participation in a clinical trial that may have effects on gastrointestinal symptoms in the preceding 4 weeks,participation in a training program for gastrointestinal complaints in the preceding 6 months, orpresentation of a sibling aged 7 to 12 years suffering from abdominal pain.

The standardized procedure of gastroenterological diagnostics is explained in more detail in the section ‘procedures’ below. In the second step, we defined inclusion criteria for study participation as follows:functional abdominal pain (FAP) presenting as functional dyspepsia, irritable bowel syndrome, functional abdominal pain or functional abdominal pain syndrome (Rome-III Criteria H2a, H2b, H2d, H2d1), andinformed written consent of parent(s) and child.

Exclusion criteria for study participation are as follows:severe internalizing psychiatric disorders with primary treatment indication, orvery limited group skills that are operationalized as severe externalizing disorders.

Sites (n = 5) were selected based on the availability of a pediatric gastroenterological consultation hours and staff experienced in diagnosis and treatment for FAP (for example, certified by the German Society for Pediatric Gastroenterology and Nutrition, GPGE). Eligibility criteria for the selection of trainers (n = 10) were expertise and occupational background for pediatric psychology, chronic pain, child psychotherapy or treatment of children with chronic diseases. All trainers received an intensive training in conducting both interventional and control training (IG and CG) during a mandatory 3-day train-the-trainer seminar.

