### Intervention and **c**ontrols

Intervention group (IG) and control group (CG) are comparable with regard to group size (3 to 8 children), number and duration of sessions for children (n = 6, 90 min each) and parents (n = 2, 50 min each). Training sessions for children are once a week. In both groups, the intervention period per patient lasts 6 weeks in the study centers, with 2 weeks pre- and postintervention being added for the pain diary. All study centers conduct both treatment approaches.

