### Analysis of secondary outcomes

Further, we will analyze primary and secondary outcome measures using a mixed model, adjusting for the therapist (random effect) and baseline measures (including age, gender, duration of illness, age at onset and the baseline measure of the outcome of interest).

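### Children are taught in training groups, but the confirmatory models treat them as independent and the supporting model adds only a therapist effect, so the claimed alpha control is not assured

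*Protocol article*

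**What the plan says.** All references are to the protocol article.

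- **Delivery.** Under Intervention and controls, the arms are "comparable with regard to group size (3 to 8 children") and in the number and length of sessions.
- **Number of groups.** Under Randomization, "Each center has to realize four different groups", and "a maximum of 25 groups are to be trained". Block sizes run from 6 to 16, which is twice 3 to 8. This fits a block that splits into one intervention group and one control group.
- **Trainers.** Ten are foreseen (Participants). The trainer may choose the arm in the first block, and "in the second block, the trainers have to change the trial arm".
- **Confirmatory models.** Under Primary analysis of the primary endpoints, an ANCOVA is specified "comparing the log area under the pain intensity curve from intervention to 12-month follow-up between the two random groups", adjusted for baseline. Episode length is handled in the same way and frequency by Poisson regression. No term for training group, therapist or centre is named.
- **Supporting model.** Under Analysis of secondary outcomes, a mixed model for primary and secondary outcomes is planned, "adjusting for the therapist (random effect) and baseline measures".
- **Error control.** Confirmatory analysis tests at 2.5% and states that the trial's overall alpha stays within 5%.
- **Sample size.** The factors listed are intervention, gender, age and site. Training group is not among them.

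**The concern.** Children are randomised individually but treated together for six sessions with the same peers and trainer. Outcomes within a training group may therefore be correlated. Because each group sits wholly in one arm, variance between groups adds directly to the variance of the arm difference. A model that takes children as independent leaves this component out of the standard error.

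The therapist random effect in the supporting model does not supply it. With 10 trainers and about 20 groups, each trainer would run on average two groups, one per arm. A therapist intercept is common to both arms and largely drops out of the contrast. What varies between groups within a therapist remains unmodelled.

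At stake are the error rate of the one confirmatory test that opens the hierarchy, and the width of the reported interval.

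**Working it through.** **Inputs from the protocol.** N = 112 (56 per arm); 5 centres × 4 = 20 groups, at most 25; 10 trainers; 20% dropout, leaving 90; d = 0.6. Mean group size m is 112/20 = 5.6 or 112/25 = 4.5.

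**Assumed.** The training-group ICC of the baseline-adjusted outcome, taken as 0.01, 0.05 and 0.10. Power is not stated either; 80% at two-sided 5% is assumed below.

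**Step 1: the plan's own figure.** With independent children, d = 0.6, two-sided 5% and 80% power, a two-sample t-test needs 45 per arm, or 90. Then 90/(1 − 0.20) = 112.5, in line with the planned 112. A repeated-measures calculation with f = 0.25 and correlation 0.8 gives 109 to 111. Both routes imply a design effect of 1.

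**Step 2: design effect and type I error.** DE = 1 + (m − 1) × ICC. The naive residual variance shrinks slightly under clustering, so the variance ratio is R = DE / [(N − 2·DE)/(N − 2)]. The actual error of the unclustered test is 2Φ(−z/√R), with z = 1.960 (5%) or 2.241 (2.5%).

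Example with 20 groups and ICC 0.05: DE = 1 + 4.6 × 0.05 = 1.23; R = 1.23/(109.54/110) = 1.235; 2Φ(−1.960/1.111) = 7.8%.

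| Groups (m) | ICC | DE | Effective N | Error at nominal 5% | Error at nominal 2.5% |
|---|---|---|---|---|---|
| 20 (5.6) | 0.01 | 1.05 | 107 | 5.5% | 2.9% |
| 20 (5.6) | 0.05 | 1.23 | 91 | 7.8% | 4.4% |
| 20 (5.6) | 0.10 | 1.46 | 77 | 10.6% | 6.5% |
| 25 (4.5) | 0.01 | 1.04 | 108 | 5.4% | 2.8% |
| 25 (4.5) | 0.05 | 1.17 | 95 | 7.1% | 3.9% |
| 25 (4.5) | 0.10 | 1.35 | 83 | 9.2% | 5.4% |

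Simulating the ANCOVA with 20 groups (20,000 runs) gave 8.2% at ICC 0.05 and 10.5% at ICC 0.10, nominal 5%.

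**Step 3: after dropout.** With 90 children, m = 90/20 = 4.5 or 90/25 = 3.6. At ICC 0.05, DE = 1 + 3.5 × 0.05 = 1.175 or 1 + 2.6 × 0.05 = 1.13. The error at nominal 5% is then 7.1% or 6.6%.

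**Step 4: variance shared by the arms.** Therapist variance crossed with arm inflates the naive standard error. In simulation with 20 groups, a therapist ICC of 0.05 alone gave 4.5% at nominal 5%. Group and therapist ICC both at 0.05 gave 6.8%, against about 8% without the therapist component.

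**Step 5: the therapist-only mixed model.** Simulated error at nominal 5% was about 9.0% (group ICC 0.05) and 11.7% (0.10). These use a Wald z reference, which gave about 6% with no clustering, so part of the excess comes from the reference distribution. The model still does not remove the inflation.

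**Step 6: with a training-group effect.** A random group effect and a t reference on 18 degrees of freedom (20 groups − 2) gave 3.2% to 4.9% at nominal 5%, and 1.3% to 2.5% at nominal 2.5%, for group ICC from 0 to 0.20.

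**Step 7: precision.** Power ≈ Φ(0.6 × √(effective N/4) − 1.96), two-sided 5%. For N = 112 in 20 groups it falls from 89% with no clustering to 87%, 82% and 75% at ICC 0.01, 0.05 and 0.10.

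**The case against.** **The ICC is unknown and may be small.** The outcome is each child's own 14-day diary, the groups meet six times, and most of the AUC period follows the end of the groups. At ICC 0.01 the excess is about half a percentage point. This stands: the size of the problem is an assumption, and only the missing variance component is a fact.

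**The stated level is 2.5%.** Neither its sidedness nor whether it covers the AUC test is clear. If it is two-sided and does cover that test, the AUC error with 20 groups stays under the 5% ceiling at ICC 0.05 (4.4%) and passes it at 0.10 (6.5%). This stands, so both levels are shown.

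**Shared centre and therapist variance works the other way.** This also stands. It reduced the inflation in Step 4 but did not remove it when the two ICCs were equal. With a small group ICC it could cancel it.

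**Clustering is partly addressed.** A therapist effect allowed to differ by arm would come close to a training-group effect when each trainer runs one group per arm. The article does not say that the effect differs by arm, and the model is in any case not the confirmatory one.

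**This is detail for the analysis plan.** It would be if the article were silent. The article, however, names the confirmatory models and the only random effect, and states that alpha is controlled.

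**Stronger readings.** A reader might infer that the type I error is inflated as a matter of fact, or that more children must be enrolled. The documents support neither. They give no ICC, and valid inference at N = 112 needs only a model that matches the delivery.

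**Conclusion.** The point holds in conditional form. The confirmatory models and the supporting model leave out the training-group level at which both interventions are delivered, and the therapist effect is crossed with arm and cannot stand in for it. The statement that overall alpha stays within 5% therefore rests on independence between children taught together, which the design does not guarantee.

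The direction requires a group ICC above zero that is not offset by variance shared across arms. The excess is slight at 0.01 and material from about 0.05. The Step 2 figures assume groups of equal size, full retention and no shared therapist or centre variance. More groups, dropout or shared variance lower them. Since the confirmatory test is affected and the remedy needs no new data from the children, the change should be made before unblinding.

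**What to change.** 1. Add a random effect for training group (nested in centre or therapist by arm), with centre as stratification factor, to the AUC model and the episode-length model. Use Kenward-Roger or Satterthwaite degrees of freedom.
2. In the Poisson model, use a group random effect or a cluster-robust variance with small-sample correction. Kenward-Roger does not carry over directly to that model.
3. In the supporting mixed model, keep therapist and add training group.
4. Restate the precision of N = 112 under an assumed ICC range: effective N about 107, 91 and 77 at ICC 0.01, 0.05 and 0.10 with 20 groups. Do not enrol more.
5. State whether the 2.5% level is one- or two-sided and whether it applies to the AUC test.

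**Cost.** A change of wording, plus a coded group identifier in the data set. The article does not say that membership is recorded, but groups are formed through the allocation, so it should be known. The interval widens somewhat. Cluster-level degrees of freedom are about 18 to 23 (20 − 2 to 25 − 2), and four fewer if the five centres enter as fixed effects. The test is slightly conservative if the ICC is near zero, and more so if shared therapist or centre variance is left out while group is fitted.

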### Outcome variables

#### Primary outcome measure

The primary outcome is the course of pain frequency and intensity of FAP (composite score) from pretreatment (T1) to post-treatment (T2), 3-month (T3) and 12-month follow-up (T4). Pain symptoms will be assessed via self-report using the pain diary, which has already successfully been implemented in prior trials [20–22]. On 14 consecutive days, children should report intensity of pain on a 10-point visual analog scale. Pain duration and frequency are derived from reports on time spans of when the pain arose.

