### Confirmatory analysis

In terms of clinical relevance, the composite pain score is the most prominent outcome: a substantial pain reduction is mandatory for treatment efficacy. We therefore apply a hierarchical testing procedure; the number and length of pain episodes will be tested only if there is a significant difference between the treatment groups in the log area under the curve (auc) of pain intensity. These endpoints will be tested to an alpha level of 2.5%; therefore, under this hierarchical design the overall alpha level of the trial will not exceed 5%.

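### The gatekeeping variable, a plain log of the post-intervention pain-intensity area, has no value for a child who is pain-free in every follow-up diary, and how such zeros are handled can decide the confirmatory test

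*Protocol article*

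**What the plan says.** Under Primary analysis of the primary endpoints the protocol states: "An analysis of covariance will be performed in the ITT population", "comparing the log area under the pain intensity curve from intervention to 12-month follow-up", adjusted for the baseline measurements. Length of pain episodes is to be analysed in the same way; frequencies get a Poisson regression. Under Confirmatory analysis, number and length of episodes are tested "only if there is a significant difference between the treatment groups in the log area under the curve (auc) of pain intensity".

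Under Primary outcome measure the data source is a diary: "On 14 consecutive days, children should report intensity of pain on a 10-point visual analog scale". The lower anchor of the scale and the score for a pain-free day are not given. The same section defines the course of pain "from pretreatment (T1) to post-treatment (T2), 3-month (T3) and 12-month follow-up (T4"), so it starts at pretreatment, whereas the analysis section starts at the intervention.

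Under Medical screening, entry requires "abdominal pain at least once per week for at least two months". Under Data analytic plan, "Missing values will be replaced by unbiased substitution (EM-algorithm").

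**The concern.** A confirmatory variable should have a value for every outcome that a child can have, above all the best one. Here a child with no pain in any follow-up diary has area 0, and the stated formula returns nothing. The entry threshold of weekly pain means about two episodes per 14-day diary, so an empty diary after treatment is foreseeable. Poisson regression copes with zero counts; the log area does not. Because episode length is analysed in the same way, the difficulty recurs for a child with no episodes.

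Someone will have to choose a rule for these children. If it is chosen after unblinding, the result of the gatekeeping test, and so whether the other pain endpoints are tested at all, can depend on that choice. If the undefined values were coded as missing and passed to the EM step, complete responders would receive modelled positive pain levels.

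**Working it through.** The protocol gives no share of children with zero area, so there is no figure of its own to reproduce on this point. What follows shows how sensitive the test is.

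**When zero area occurs.** All of these must hold: pain-free days score 0; T1 is outside the area; T2, T3 and T4 are all pain-free. One painful day makes the area positive. The analysis section implies the second condition, since it starts at the intervention and adjusts for baseline; the outcome section, starting at T1, points the other way.

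**Inputs.** From the protocol: 56 per arm. Assumed: non-zero time-averaged pain score log-normal with median 3 and log-scale SD 0.6; a two-sided 5% test, counting rejections that favour the intervention; no covariate. A zero is replaced by log(c), where c is the offset.

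**Scenario 1: zeros 25% (intervention) v 10% (control), no other effect.**
- Zeros dropped: 56 × 0.75 = 42 v 56 × 0.90 = 50.4 children remain, with identical distributions. Difference 0.00, favourable rejection 2.5%.
- c = 0.001: a zero becomes log(0.001) = -6.91, against a mean of log 3 = 1.10 for the rest, a gap of 8.01. Difference = -(0.25 - 0.10) × 8.01 = -1.20. Variance per arm = p(1-p) × gap² + (1-p) × 0.36 (p = share of zeros), i.e. 12.29 and 6.09. SE = √((12.29 + 6.09)/56) = 0.573; z = 2.10; favourable rejection about 55% (simulated 54%).
- c = 1: a zero becomes 0, and the mean of log(1 + score) for the rest is 1.42. Difference = -0.15 × 1.42 = -0.21. SE = √((0.525 + 0.358)/56) = 0.126; z = 1.70; about 40% (simulated 38%).

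The differences -1.20 and -0.21 are on different scales and are not a range for one effect; the rejection rates are comparable.

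**Scenario 2: zeros 5% in each arm (about 3 children per arm), log shift -0.35 among the rest.**
- Dropped: 53.2 per arm; SE = 0.6 × √(2/53.2) = 0.116; z = 3.01; 85%.
- c = 0.001: difference = -0.95 × 0.35 = -0.33; SE = √((3.13 + 3.39)/56) = 0.341; z = 0.97; about 16% (simulated 17%).
- c = 1: difference -0.233; SE = √((0.220 + 0.282)/56) = 0.095; z = 2.46; about 69% (simulated 68%).

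**Second model.** Baseline-adjusted ANCOVA, log-scale SD 0.8, baseline correlation 0.5, non-zero control median 1.5, 4000 runs, two-sided 5%. Rejection rates:

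| Zeros IG v CG; log shift | drop | c = 0.001 | c = 0.1 | c = 1 | rank | untransformed |
|---|---|---|---|---|---|---|
| 15% v 5%; none | 5% | 38% | 29% | 18% | 17% | 11% |
| 30% v 10%; none | 6% | 74% | 65% | 48% | 49% | 27% |
| 10% v 10%; -0.35 | 70% | 12% | 33% | 50% | 50% | 50% |
| 15% v 5%; -0.35 | 72% | 71% | 85% | 86% | 86% | 76% |
| no zeros; -0.35 | 75% | 75% | 75% | 73% | 73% | 61% |

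Without zeros the log-based choices agree. With a few zeros they separate, and no choice is best throughout.

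**The unit matters too.** Adding 1 to an area accumulated in score-days over about 365 days equals c = 1/365 = 0.0027 on the daily-average scale, close to the very small offsets above. Naming an offset without naming the scale would not settle the question.

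**The case against.** The strongest reply is that the problem may never arise. It needs a zero-anchored scale, T1 outside the area and three wholly pain-free diaries. If pain-free days score 1, or T1 counts (weekly pain at entry makes an empty baseline diary very unlikely), zeros vanish or become very rare. Diaries are also kept during the intervention in both arms, and the Blinding section says the intervention-specific diary data will join the data set; if they enter the area, zeros become rarer still. An offset could also sit in an analysis plan that is not shown. These points limit how often the failure occurs. They do not remove it, because the text leaves each condition open and the formula that it fixes is the plain log.

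A reader might infer that the best responders drop out and that the comparison is therefore biased toward no effect. The documents do not support this. No section excludes or recodes a zero, the analysis is by intention to treat, and the EM rule covers missing values, whereas a completed pain-free diary is observed. Exclusion and imputation are possible readings, not stated rules. The complete loss of effect in scenario 1 follows from placing all the benefit in the zeros. With a log shift of -0.35 among the rest and zeros of 5% v 2% or 10% v 5%, dropping them gives 84% and c = 1 gives 85% and 83%; only the very small offset does badly (c = 0.001: 53% and 44%).

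It is also fair to say that the untransformed score is no simple cure: about 19% favourable rejection in scenario 1, the lowest among the options that keep every child.

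**Conclusion.** The concern holds in a conditional form. The gatekeeping variable is a log of a quantity that can be zero, it is undefined for a child pain-free at T2, T3 and T4 under the reading that the analysis section implies, and episode length shares the defect. Under assumed zero shares of 5% to 25%, the handling of zeros moves favourable rejection from 2.5% to 54% in scenario 1 and from 17% to 85% in scenario 2. These sizes rest on the assumed shares and log-normal scores; the protocol supplies neither. The direction of any distortion is not fixed: dropping zeros hides a benefit that lies in the zeros, yet gives the highest rejection when zeros are equal in the two arms. The point is worth settling before analysis because it concerns the test on which the other pain endpoints depend.

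**What to change.** Before unblinding, state in the protocol or analysis plan:

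1. A completed pain-free diary is scored 0 and is never treated as missing; give the lower anchor of the scale.
2. The area covers T2 to T4, with T1 as covariate only; bring the outcome and analysis sections into line, and say that diaries kept during the intervention are outside the area.
3. Replace the plain log area by one form defined at zero: log(1 + time-averaged daily pain score), with the average on the diary's own scale so that the offset has a fixed meaning.
4. Apply a form defined at zero to episode length as well.
5. Report other offsets, rank-based ANCOVA and untransformed ANCOVA as sensitivity analyses.

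The cost is a few sentences and no new data. The treatment effect is no longer a pure ratio. Power is a little lower where there are no zeros (73% v 75% in the second model), and lower than with a very small offset where the benefit lies wholly in the zeros (38% v 54% in scenario 1). In return, every child has a value and the choice is made before the arms are known.
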